## **5.3 Escape medication**

Medical indications or international guidelines about intervention after surgery are lacking. The decision to start any co-intervention will be based on the participants' experience of vertigo attack frequency and patient-doctor preference (shared decision-making). Shared decision-making ensures wide applicability of study results and reflects daily medical practice. The protocol for frequency and methods of IT injections can be found in the appendix (Appendix 4).

The use of metoclopramide in an acute phase of vertigo is allowed. The following dosages will be prescribed:

- Metoclopramide oral or rectal with a maximum of 30 mg per 24 hours  
and/or
- Betahistin with a maximum of 48 mg per 24 hours or cinnerrazine with a maximum of 75 mg per 24 hours  
and/or
- Ondansetron with a maximum of 16 mg per 24 hours

Moreover, intervention may be carried out after surgery if the patient continues to suffer from vertigo attacks. This may be intratympanic injections of corticosteroids or in exceptional cases, ablative surgery such as vestibular neurectomy and labyrinthectomy. This is offered when the bouts of vertigo are intolerably frequent.

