#### 8.1.2 Secondary study parameters

- Cumulative incidence of vertigo bouts
- Hearing
  - As defined in the diagnostic criteria of the Bárány Society (Lopez-Escamez, 2016), the following parameters will be assessed based on a three-tone audiometry at 0.5, 1 and 2 kHz (LFI):
    - The three-tone average score in decibels (dB), labelled as hearing threshold (HT).
    - Word recognition (WR), based on the speech discrimination. A decrease of  $\geq 10$  dB or a change in word recognition score of  $\geq 15\%$  points is considered clinically significant. When the pure-tone average and the WR change in the opposite direction, the pure-tone average score will be decisive to conclude the overall nature of change in hearing.
  - All pure tone audiometry analyses will be executed by the participating centre itself.
- Use of escape medication
  - The frequency and use of escape medication in the acute phase of vertigo will be recorded. This includes intratympanic injections and antivertigo medication.
- Co-interventions
  - Co-intervention is defined as performed ablative surgery during the follow up period because of unbearable vertigo bouts.
- Complications of surgery
- Functional Level Scale (FLS)
  - To assess the effect of the vertigo attacks on daily life, the 6-point FLS is recommended by the AAO-HNS for clinical trials in MD (Committee on Hearing and Equilibrium guidelines for the diagnosis and evaluation of therapy in Ménière's disease, 1995). One value is chosen to score the level of disability. The score will be reported as a total score, as

well as categorized into improvement, unchanged or worsened.

Categories will be based on the following definitions:

- Improvement: one or more points decrease on the FLS score compared to the baseline FLS score
- Unchanged: unchanged FLS score compared to the baseline FLS score
- Worsened: one or more points increase on the FLS score compared to the baseline FLS score.

- Dizziness Handicap Index (DHI)

- To evaluate the effect of vertigo in the patient's daily life the 25-item measure of the DHI is used which was developed by Jacobson and Newman (1990). This inventory is often used for follow-up of participants suffering from dizziness. Higher scores indicate more severe handicap. According to a review published in 2007 (Duracinsky 2007) it is a valid tool and could be regarded as a questionnaire of reference.
- The outcome is categorized as following:
  - 0-16 points: no handicap

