#### **10.2.2 Computation of outcome**

All secondary outcomes will be analysed using a linear mixed model (EDB vs decompression group) at the different time measurement point.

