#### **12.6.1 Data analysis and release of results**

The data from the trial will be centrally analysed from Participating Centres by the trial statistician.

We plan to use non-parametric tests in the analysis of the data. Non-parametric methods are more robust as they make fewer assumptions (distribution of the data). As a downside non-parametric are less efficient, i.e. they need a higher sample size to achieve the same power. As a compensating factor we use the relative efficiency of the Mann-Whitney U-test as compared to the t-test which has been estimated as 95% (Conover 1999, Practical Nonparametric Statistics).

In order to estimate a realistic treatment effect that avoids bias due to treatment-arm crossover and selective drop-out, an intention-to-treat analysis will be conducted as the primary analysis.

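### One linear mixed model is fixed for every secondary outcome, including counts and one-off yes/no events that it does not suit, and section 12.6.1 announces a conflicting non-parametric plan

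*Protocol*

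**What the plan says.** Section 10.2.2 of the protocol gives one rule for the secondary outcomes: "All secondary outcomes will be analysed using a linear mixed model (EDB vs decompression group) at the different time measurement point".

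Section 8.1.2 shows what that rule has to cover:

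- Counts: "Cumulative incidence of vertigo bouts", and escape medication, for which "The frequency and use of escape medication in the acute phase of vertigo will be recorded".
- One-off yes/no events: surgical complications and co-intervention. "Co-intervention is defined as performed ablative surgery during the follow up period because of unbearable vertigo bouts". Section 5.3 expects such surgery only "in exceptional cases, ablative surgery such as vestibular neurectomy and labyrinthectomy".
- Three-level response categories derived from the FLS, DHI and THI.
- Repeated scores and measurements: questionnaires, hearing, gait.

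Section 10.2 checks normality only for the patient-reported measures, and the check decides only whether means or medians are shown. For categorical outcomes it gives counts and percentages and names no test.

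Section 12.6.1, in the publication chapter, says something different: "We plan to use non-parametric tests in the analysis of the data". It accepts a loss of efficiency and adds: "As a compensating factor we use the relative efficiency of the Mann-Whitney U-test as compared to the t-test", put at 95%.

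**The concern.** There are two faults, and both lie in what the protocol states rather than in what it leaves open.

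First, 10.2.2 applies a model for repeated, roughly Gaussian measurements to outcomes of other kinds. Ablative surgery and complications give one value per patient, so there is no within-patient series to model. Counts and ordered categories are not Gaussian.

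Second, 12.6.1 plans another family of methods. The primary outcome is a proportion tested by chi-square or Fisher (section 10.1), so a Mann-Whitney versus t-test argument can only concern the secondary outcomes, which 10.2.2 has already assigned to the mixed model.

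At stake is whether each secondary result comes from one pre-specified analysis. With both statements standing, the method could be chosen after the data are seen.

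**Working it through.** **1. The 95% factor and the sample size.** The efficiency of Mann-Whitney relative to the t-test for normal data is 3/π = 0.955, which agrees with the 95% in 12.6.1. Section 4.4 takes 32 per arm for 95% versus 70%, adds 5 per arm for loss, and reaches 32 + 5 = 37 per arm and 74 in total. An allowance of 95% would have given 32/0.95 = 33.7, so 34, then 34 + 5 = 39 per arm. The factor is therefore not in the stated total, and it has no role in comparing two proportions. (Two-sided Fisher at 32 per arm has a computed power of 68.0%, not 80%. That is a separate matter and nothing below depends on it.)

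**2. One-off events, single tables.** With one row per patient a linear mixed model reduces to a two-sample linear comparison. For 0/37 versus k/37 the pooled variance is v = k(1 − k/37)/72, the standard error of the difference is √(2v/37), and t = (k/37)/SE on 72 degrees of freedom. Fisher's two-sided p is 2·C(37,k)/C(74,k).

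- k = 4: v = 4 × 0.8919/72 = 0.04955; SE = 0.05175; t = 0.1081/0.05175 = 2.089; p = 0.040. Fisher: 2 × 66,045/1,150,626 = 0.115.
- k = 5: v = 0.06006; SE = 0.05698; t = 2.372; p = 0.020. Fisher 0.054.

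For k = 4, the 95% interval for the arm with no events is 0 ± 1.993 × √(0.04955/37) = −7.3% to +7.3%, which is impossible for a proportion.

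**3. One-off events, type I error.** Exact enumeration over all tables, 37 per arm, two-sided 5%:

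| True event rate | Linear | Fisher |
|---|---|---|
| 1% | 0.07% | 0.0% |
| 2% | 0.6% | 0.01% |
| 4% | 2.8% | 0.15% |
| 5% | 3.9% | 0.3% |
| 10% | 5.8% | 1.5% |
| 15% | 5.3% | 2.3% |

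The protocol's own rates (section 9.2.1) span this range: under 4% for permanent hearing loss and 10 to 15% for minor CSF leakage.

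**4. Counts.** The protocol gives no mean or dispersion, so the following are assumptions: 37 per arm, variance μ + kμ². The t-test stands in for the mixed-model contrast. A fitted random-intercept model on three visits (about 270 runs per scenario) agreed with it, for example 83% power for both at k = 2 and rate ratio 0.33.

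Type I error of the linear test was 4.1 to 5.1% for negative binomial counts (32 to 37 per arm) and 3.8 to 4.6% for zero-heavy counts.

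Power:

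| Scenario | k | Linear | Mann-Whitney | Negative binomial |
|---|---|---|---|---|
| Zero-heavy: 95%/70% with no attacks, mean 6 in the rest | 0.5 | 65% | 82% | not run |
| | 1 | 54% | 77% | not run |
| | 2 | 39% | 68% | not run |
| Plain rate reduction: mean 6, rate ratio 0.33 | 1 | 98% | 94% | 98.5% |
| | 2 | 82% | 67% | 86.5% |
| | 4 | 50% | 35% | 62.5% |

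In the zero-heavy case the linear test loses 82 − 65 = 17, 77 − 54 = 23 and 68 − 39 = 29 points. Under a plain rate reduction it gains 4, 15 and 15 points over Mann-Whitney. The negative binomial test had a type I error of 5.5 to 7.5% (400 runs), so its power is slightly flattered.

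**The case against.** **The linear test is not shown to be invalid.** A reader might infer from 0 versus 4 events that the linear model is anti-conservative for rare safety events. The enumeration does not support this: the error is well under 5% at rates up to 4%, and the largest value in the table is 5.8%, at 10%. Nor is Fisher the truth here. For 0 versus 4, Barnard's unconditional exact test gives 0.047 and Boschloo's 0.081; for 0 versus 5, Barnard gives 0.027. Much of the gap is Fisher's conservatism. This objection stands in full.

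**Loss of power is not general.** A reader might also infer that the linear model wastes power on counts. That depends on the zero-heavy scenario, which borrows the shares assumed in 4.4 for being attack-free at 12 months. The secondary count covers the whole first year, so a patient attack-free at 12 months may have had earlier attacks. Under a plain rate reduction the ranking reverses. This stands too.

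**Unequal diary time may already be handled.** Section 10.1.1 imputes the daily app data to complete data sets. It sits under the primary outcome, but the attacks come from the same diary, so a count method has to fit with it.

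**The 95% sentence distorts no number.** True: 12.6.1 does not say that the factor entered 4.4, and step 1 shows that it did not. It is a leftover that misdescribes the plan.

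**Such detail belongs in a statistical analysis plan.** Covariates and model options do. But 10.2.2 does not leave the method open: it fixes one for all secondary outcomes, and 12.6.1 contradicts it. Reading non-parametric as a loose reference to Fisher's test does not help, because the justification given is "the relative efficiency of the Mann-Whitney U-test as compared to the t-test which has been estimated as 95" per cent.

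**Conclusion.** The point holds as a badly fixed rule plus an unreconciled contradiction. Section 10.2.2 imposes a linear mixed model on counts, one-off events and response categories that it does not suit, and 12.6.1 plans a different analysis for the same outcomes. The method matters at this sample size: with 37 per arm, 0 versus 4 events falls on either side of 5% (0.040 linear, 0.115 Fisher).

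The documents do not support a claim that the linear model generally gives wrong p-values or loses power. Its error rates are near or below nominal, and whether it beats a rank test depends on a count distribution that the protocol does not give. That dependence is itself a reason to settle on one method in advance.

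For questionnaire scores, hearing and gait the mixed model is reasonable. The matter is confined to secondary outcomes. It should be corrected, but it does not touch the primary test or the sample size.

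**What to change.** - In 10.2.2, limit the linear mixed model to repeated continuous outcomes: questionnaire scores, hearing and gait.
- For attack and escape-medication counts, name one method: a negative binomial model or a rank test of rates. State how it uses the diary data, consistently with the imputation in 10.1.1. If the negative binomial is chosen, check its type I error at this sample size.
- For ablative surgery and complications, name an exact or stratified test. For the improved/unchanged/worsened categories, name an ordinal or categorical method.
- In 12.6.1, delete the non-parametric and 95% efficiency sentences, or limit them to any outcome for which a rank test is the chosen method.

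The cost is protocol wording and a few more model types in the analysis program. No new data or patients are needed.

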### **10.3 Other study parameters**

NA

### **10.4 Interim analysis**

An interim analysis of the data for the first 21 participants will be performed after 6 weeks follow up of the 21st surgery. The DSMB will discuss the safety of the participants, and advice whether or not to continue the study.

## **11. ETHICAL CONSIDERATIONS**

### **11.1 Regulation statement**

The study will be conducted according to the principles of the Declaration of Helsinki (October 2013) and in accordance with the Medical Research Involving Human Subjects Act (WMO, 26 February 1998) and the International Conference on Harmonization Good Clinical Practice (ICH GCP, November 2016). The study will be conducted in compliance with the protocol.

### **11.2 Recruitment and consent**

Patients with MD meeting the inclusion criteria will be asked to participate in the study by their ENT specialist in the PC. Consent to enter the study must be sought from each participant only after a full explanation by the ENT specialists of the PC has been given, an information leaflet offered, and time allowed for consideration (one month at maximum). Patients will especially be informed that two slightly different surgical procedures will be performed.

Patients are allowed to contact the independent expert for any questions. Signed participant consent should be obtained. The ENT specialists of the PC also signs the consent form. The right of the patient to refuse to participate without giving reasons must be respected at all times throughout the trial.

### **11.3 Objection by minors or incapacitated subject**

Not applicable.

### **11.4 Benefits and risks assessment, group relatedness**

Both the EDB and decompression surgery are not without its risks.

A mastoidectomy and identification of the endolymphatic duct could lead to meningitis, hearing loss, facial nerve palsy, labyrinth function loss. Meningitis and facial nerve palsy have not been reported (nor literature nor in the pilot groups operated in Antwerp by [name]). Mild hearing loss has been seen in 2 patients in our pilot. Three patients of the pilot group treated with EDB suffered drop attacks, but recovered within 8 weeks. Moreover, in three patients operated in Antwerp, postsurgical CSF leakage occurred, but successful surgical reintervention was performed the next day.

Benefits for the participants in this study are that 50% of the participants will undergo EDB surgery of which we believe (based on the previously discussed results of EDB) that it will effectively treat their vertigo attacks. Of the participants in the decompression group, an

estimated 70% will benefit from the surgery. Therefore, only 30% of the decompression group (n = 13, 15% of the total study population) will not directly benefit from participation in the study.

Furthermore, if at the end of the study these participants would still be eligible for EDB surgery and results are in favour of the EDB procedure, EDB surgery can be performed in less time with less trauma and risk, since the access to the ED through the petrous bone has already been established during the decompression operation.

Depending on the group the participant is in, 2 or 3 CT scan will be performed.

In the EDB group, one CT scan will be performed preoperatively to assess the course of the endolymphatic duct, which is helpful preoperatively in finding the duct. After placement of the clip, a CT scan is performed to assess the clip position. After deblinding, a third CT scan can be performed to assess clip position, but only if the participant still has vertigo attacks.

In the endolymphatic sac decompression group, the same preoperative CT scan will be performed. The same peroperative CT-scan is performed to assess if structures were correctly identified.

Each performed CT scan leads to exposure to ionizing radiation: approximately 2 mSv per scan. For reference: the background radiation in the Netherlands is approximately 2.5 mSv per year.

### **11.5 Compensation for injury**

The sponsor/investigator has a liability insurance that is in accordance with article 7, subsection 6 of the WMO. This is through the insurance company of the HagaHospital (Centramed). The sponsor also has an insurance, which is in accordance with the legal requirements in the Netherlands (Article 7 WMO and the Measure regarding Compulsory Insurance for Clinical Research in Humans of 23th June 2003). This insurance provides coverage for damage to research participants through injury or death caused by the study. The insurance applies to the damage that becomes apparent during the study or within 4 years after the end of the study.

### **11.6 Incentives**

None.

## **11.7 Other ethical considerations**

### **11.7.1 Support of other relevant communities**

Support of relevant patient community, the Dutch ENT Society (KNO-vereniging) and the vertigo centres is obtained. The relevant patient community has endorsed the protocol and the patient information. Their written support can be found in this dossier in Chapter K, 'Overige documenten'.

## 12. ADMINISTRATIVE ASPECTS, MONITORING AND PUBLICATION

### 12.1 Handling and storage of data and documents

#### - Castor EDC

Data storage will be done in Castor, which provides electronic data capturing. Castor is secured according to the most recent standards in order to protect data and is certified for ISO 27001 (Standards for Information Security Assurance). The handling of personal data will be in compliance with the EU General Data Protection Regulation and the Dutch Act on Implementation of the General Data Protection Regulation (in Dutch: Uitvoeringswet AVG, UAVG).

Building of the database in Castor will be done by the coordinating investigator initiating centre (HagaZiekenhuis) under supervision of a trained data manager. The coordinating investigator will have access to all patient records of the participating centres. She will be the only individual to enter data into Castor EDC.

In case of unexpected, long-term absence of the coordinating investigator, the data entry will be performed by the local investigators. Access to the database and rights for data entry of only their own centre will be provided before the start of the trial.

Per centre, a subject identification list will be safeguarded by the main investigator of the centre. The local study team can access this file. Coding of participants will not include patient initials or birthdate.

The coordinating investigator will have (secured, remote) access to the patient files of each participating centre. All data will be extracted from the patient records and recorded in Castor EDC.

The MRI scans will be sent on a CD-ROM by registered mail (as is usual clinical practice) to the HagaHospital for double assessment. After scanning in the images, the CD-ROM will be destroyed. The second radiologist will assess the images in the HagaHospital and note the findings in the records of the HagaHospital. From there, the coordinating investigator will record the data in Castor.

The only persons having access to the source data will be the local investigator, the local study team, the coordinating investigator, the monitor and possibly the inspector.

The only person having access to Castor EDC is the coordinating investigator and possibly researches from the local study team. All persons with access to Castor EDC will have

access restricted to only the necessary parts of Castor, i.e. only to the data of patients from their own centre. Moreover, there will be one other person with access to the data, for the case of unexpected events (such as unavailability of the coordinating investigator). Access to the data will be logged, and apart from a short training, this person will not be looking into the data. This 'back up' person will be [name], ENT-surgeon in the HagaHospital, who is not in any other way involved in the trial.

All data will be stored in Castor for 15 years after the last subject has had the last study visit. The servers are located in Amsterdam.

Members of the research team will be informed in case record retention is prolonged or when records are no longer needed.

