Patients will be included in one of the 7 centres that take part in this study. There will be baseline questionnaires, imaging and testing. There will be a standard preoperative screening by the anaesthetist. The surgery will take place in the centre where the patient is included and where the follow up takes place, unless the local researcher prefers to perform surgery in the HagaHospital (due to experience with the surgery).

After surgery, there will be follow up visit at 1 week, 3 months, 6 months and 12 months after surgery. Throughout this period, patients will continuously report daily functioning and vertigo attacks in the DizzyQuest app. Moreover, the patient is treated by a vestibular therapist in the first 3 months after surgery.

After one year of follow up, both patient and the follow up ENT-surgeon are deblinded. If the patient was allocated to the EDB group, a CT-scan will be performed to assess if the clip is correctly in place if the patient still suffers attacks.

If the results of this trial are in favour of EDB, patients in the decompression group who still suffer vertigo attacks will be offered EDB when the last patient has been deblinded.

An extensive flow chart, including all the questionnaires and tests that will be performed, can be found in the appendix (Appendix 2).

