## 4. STUDY POPULATION

### 4.1 Population (base)

Patients with MD will be recruited in all 7 centres. These patients will typically be under treatment by one of the participating centres. Those patients meeting the inclusion/exclusion criteria will be informed by their ENT-surgeon. Below an estimate is provided per centre of the number of patients eligible for this study based on historic data.

| Centre                                               | Expected number of patients eligible for study |
|------------------------------------------------------|------------------------------------------------|
| Beatrix Ziekenhuis, Gorinchem                        | 2                                              |
| Gelre Ziekenhuizen - Apeldoorns Duizeligheidscentrum | 2                                              |
| HagaZiekenhuis Den Haag                              | 62                                             |
| Leids Universitair Medisch Centrum                   | 2                                              |
| Maastricht UMC                                       | 2                                              |
| Medisch Centrum Leeuwarden                           | 1                                              |
| Wilhelmina Ziekenhuis Assen                          | 3                                              |

Based on these estimates, we expect to be able to recruit the total number of 74 patients within the 2 years in which inclusion is planned. There will not be a set number of inclusion per centre: inclusion will happen according to 'first come first serve' principle, which means that inclusion will be competitive.

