### **8.2.2 Blinding of randomisation and follow up**

The ENT surgeon responsible for follow up will be blinded as he/she has left the OR when randomisation and possible clipping took place. The ENT surgeon will be blinded until debinding at 1-year follow up of the last patient.

The coordinating investigator will take care of the follow up of the patients in the HagaHospital and will be blinded for these cases.

The patient will be blinded until the last patient is followed up for 1 year.

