### **8.3.2 Surgical procedure (T=0)**

Surgery takes place either at the site of inclusion, or in the HagaHospital. This depends on preference of the local researcher, and availability of equipment at the site. If surgery is performed at the HagaHospital, the local researcher (who has included and will follow the patient) is welcome to join the surgery. An experienced ENT-surgeon who has performed at least 20 EDB procedures ([name]) will always attend surgery to ensure there are not intraoperative differences that may induce differences in outcome. Moreover, this facilitates blinding of the follow-up surgeon.

The surgical procedure is described in chapter 5 'Treatment of participants', 5.1

Investigational product, subheading 'surgical procedure in EDB group'. The randomisation for a clip or decompression operation will be performed using the automated telephone randomised service from Castor. The outcome of randomisation and placing of clip (only EDB) will be documented in Castor. For the purpose of 'implantenregistratie', all used clips and their LOT-number must be documented. Normally, this registration takes place in the electronic patient files, but for blinding purposes, this will now be documented in a paper notebook. After completion of the trial and debinding, this information will be added to the electronic patient file.

An interim analysis of the data for the first 21 participants 6 weeks after surgery will be performed. The DSMB will assess the results and discuss the outcome, and give advice whether or not to continue the study.

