### **8.3.3 Postoperative procedures**

- One week after surgery (T+1)

One week after surgery, the patient will visit the ENT-surgeon for regular post-operative care. A vHIT will be performed. Moreover, the patient will visit the vestibular therapist whom will commence treatment. A balance test, dynamic visual acuity and gait analysis will be performed. Exercises that should be performed at home by the patient are explained. In the

following weeks, the patients carries these exercises out at home, and visit the vestibular therapist three times with two weeks in between the visits.

As surgery is currently not a normal medical treatment, this visit and these measurements are all extra for this study.

- Three months after surgery (T+2)

At three months after surgery, a follow up visit is planned at the ENT-surgeon. A vHIT is performed. The patients visits the vestibular therapist who performed measurements who finishes treatment and performs measurements. An MRI-scan and PTA are performed. The patients receives a survey package through email, consisting of the DHI, THI, FLS, EQ-5D VAS, SF-36, iMCQ and iPCQ.

This visit and these measurements/tests are all extra for this study.

- Six months after surgery (T+3)

At six months after surgery, a follow up visit is planned at the ENT-surgeon. A vHIT is performed. The vestibular therapist performs measurements. A PTA is performed. The patients receives a survey package through email, consisting of the DHI, THI, FLS, EQ-5D VAS, SF-36, iMCQ and iPCQ.

This visit and these measurements/tests are all extra for this study.

- Twelve months after surgery (T+4)

At twelve months after surgery, the last follow up visit for this trial is planned. A vHIT is performed, as well as a PTA, an MRI-scan and calorigram. The vestibular therapist performs measurements and the patients receives a survey package through email consisting of the DHI, THI, FLS, EQ-5D VAS, SF-36, iMCQ, iPCQ, VADL and VAP. If the patient was in de EDB-group, a CT-scan will be performed to assess if the clip is in place in the patients still suffers attacks. If results are in favour of EDB, and patients still suffer attacks, the patients in the decompression group will be offered EDB surgery.

This visit and these measurements/tests are all extra for this study.

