#### - DizzyQuest app

There will be a 'verwerkingsovereenkomst' between the HagaHospital and the builder of the DizzyQuest App (Psymate) in which all handling of data will be recorded. Data in the DizzyQuest app will be stored on the smartphone of the user until a stable internet connection is established. Data saved on the smartphone is encrypted and not accessible for third parties. When the smartphone connects to the internet, data will be transferred to the servers of Smart eHealth, located in Belgium. After transfer of the data, all data will be deleted automatically from the smartphone.

The coordinating investigator will monitor appliance to the DizzyQuest app. Every night, the servers generate an automatic email that is sent to the coordinating investigator, containing general information on status of participants. Therefore, if participants miss questionnaires, this will be detected and the participant will be contacted through phone or email.

The only person having access to all the data from the app is the coordinating investigator. Here too [name] will have access for the case of unexpected events. Access to the data is logged. The administrator of the database will have access to the data for quality and security control. However, email-addresses of the patient cannot be seen by the administrator. All access provisions are specified in the 'verwerkingsovereenkomst'.

After termination of the one-year follow up period, participants can delete the DizzyQuest app from their smartphone. When the app is deleted, all data are deleted from the phone as well. All data will be safely transferred to the servers of the HagaHospital after termination of the trial. Here, data will be saved for 15 years. This will be recorded in the processing agreement between PsyMate and the HagaHospital.

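### The protocol does not secure the follow-up investigator's blind and gives two different times for unblinding

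*Protocol*

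**What the plan says.** **Who is blinded.** Section 8.2.2: "The coordinating investigator will take care of the follow up of the patients in the HagaHospital and will be blinded for these cases".

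**Who enters data.** Section 12.1 (Castor EDC) says of the coordinating investigator: "She will be the only individual to enter data into Castor EDC". She has access to the records of all participating centres. Local investigators enter data only if she is absent unexpectedly and for long, but their own-centre rights are granted before the trial starts.

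**What is entered.** Section 8.3.2: "The outcome of randomisation and placing of clip (only EDB) will be documented in Castor". The sentence does not say by whom. Clip lot numbers, by contrast, go into a paper notebook until the trial is over, to protect the blind in the electronic patient file.

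**Her contact with outcome data.** She receives a nightly status email from the app, and 12.1 says that "if participants miss questionnaires, this will be detected and the participant will be contacted through phone or email". Section 12.2 gives her compliance monitoring and the transfer of app data into Castor. Section 10.1.2 derives the primary outcome from those data.

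**When unblinding happens.** Section 3 (flow chart): "After one year of follow up, both patient and the follow up ENT-surgeon are deblinded". Section 8.2.2: "The patient will be blinded until the last patient is followed up for 1 year", with the same limit for the follow-up surgeon. Section 3 (duration) also waits until one year after the last patient's surgery. Section 8.3.3 lists under the 12-month visit: "If the patient was in de EDB-group, a CT-scan will be performed to assess if the clip is in place", conditional on continuing attacks. Section 11.4 places that scan after unblinding.

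**The concern.** Taken together, the sentences on data entry, allocation recording and follow-up assign one person duties that conflict unless something keeps the allocation from her, and the protocol names nothing that does. This matters because the trial's justification is blinding: section 1 treats the absence of double-blind assessment as the decisive weakness of the earlier EDB trial, and section 3 cites improvement in 70% of patients after any surgical intervention.

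Someone who knows the allocation could, without intending to, follow up patients or pursue missed app entries differently by arm. As follow-up clinician she would also take part in the shared decisions on co-intervention in 5.3.

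On timing, centres cannot follow both unblinding rules. Under the earlier one, allocations become known while the trial is still running, and nothing requires the 12-month measurements to be complete first.

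**Working it through.** **1. How many participants are concerned.** Inputs: the centre table in 4.1, row "HagaZiekenhuis Den Haag" and the six other centres.

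- Reproducing the plan's total: 2 + 2 + 62 + 2 + 2 + 1 + 3 = 74, as stated.
- Share at the HagaHospital: 62 / 74 = 83.8%.
- Share elsewhere: 74 − 62 = 12, and 12 / 74 = 16.2%.

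These are expected shares, since 4.1 sets no number per centre.

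**2. Does anything keep the allocation from her?** There are three candidates:

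- *Access limits in 12.1.* Users see only the parts of Castor they need, but the text explains this as own-centre data. For the HagaHospital patients that does not help, because they are the patients she follows, and she has access to all centres anyway.
- *The paper notebook in 8.3.2.* It keeps clip registration out of the electronic patient file. It does not cover the randomisation result and clip placement, which the same section sends to Castor.
- *Automatic recording.* The randomisation service is Castor's own, so the allocation may be logged without manual entry. That would settle who enters it, but not who can view it.

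None of the three hides the field.

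**3. Is there a route to the primary outcome?** Patients enter attacks in the app themselves. Section 10.1.2 expects that missing entries can be imputed as attack free. A missed entry left alone would therefore tend to count as attack free, while one that is followed up may reveal an attack. If follow-up of missed entries differed by arm, the endpoint could shift. The documents give no figure from which to size this, so none is offered.

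**4. The unblinding times compared.** Inputs: all operations within 2 years of the first (Summary, study design) and 12 months of follow-up per patient. Time is counted from the first operation.

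- Rule in section 3, flow chart, for the first patient: month 12.
- Rule in section 3, duration, and in 8.2.2: up to month 24 + 12 = 36.
- Largest gap: 36 − 12 = 24 months.

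The flow-chart text later refers to the moment when the last patient has been unblinded, which fits a staggered reading.

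**5. The EDB-only CT.** Its listing under the 12-month visit in 8.3.3 is compatible with 11.4 only if unblinding has already happened by that visit. Under 8.2.2 it has not, except possibly for the last patient. These passages must be reconciled.

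**The case against.** The strongest reply is that exposure is inferred, not stated. Section 8.3.2 names no one as recording the allocation. Section 12.1 describes her data entry as extraction from patient records, and the notebook keeps clip registration out of those records. The contact about missed entries is triggered by an automatic email, and nothing suggests it would differ by arm. All of this is fair, and it rules out saying that she will be unblinded. It does not show that she is protected: section 12.1 makes her the sole person to enter data, and no provision withholds the field.

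Three stronger readings are tempting but not supported:

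- *That the double blind fails.* Under either rule patients remain blinded through their own 12 months, and the primary outcome is what they enter in the app. At the other centres (12 of 74 expected) follow-up is by someone else.
- *That both section 3 and 8.3.3 unblind each patient at 12 months.* Only the flow-chart text in section 3 states it. Section 8.3.3 mentions a conditional scan, which 11.4 places after unblinding, and the same paragraph includes the offer of EDB if results favour it, a step that can only follow the trial's end.
- *That a bias of a given size can be attached.* No figure in the protocol supports one. Nor does unblinding one patient by itself reveal another's allocation, and contamination of the 12-month questionnaires would require unblinding before they are completed, an order the text does not fix.

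**Conclusion.** The concern stands in a limited form. As written, the protocol lets a person who must stay blinded enter or see the allocation, for an expected 62 of 74 participants (84%), and that person also handles compliance with, and transfer of, the primary-outcome data. It also contradicts itself on when unblinding occurs, by up to 24 months for the first patients.

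This rests on three assumptions: that the sole-entry sentence in 12.1 means what it says, that no undocumented restriction hides the allocation field, and that enrolment is roughly as 4.1 expects. If Castor logs the allocation automatically and already hides it, the first part reduces to a missing sentence. The contradiction on timing does not depend on these assumptions, although the 24 months is an upper limit that applies if operations span the full two years.

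These are contradictions within the protocol, not details left to an analysis plan. In a trial designed to supply the blinding its predecessor lacked, they should be corrected.

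**What to change.** - **8.3.2 and 12.1:** state that the randomisation result and clip fields are recorded automatically by the randomisation service, or by the unblinded operating surgeon, in a restricted Castor form. State that the form is hidden from the coordinating investigator and all follow-up clinicians, including local investigators with own-centre rights, until the last patient's 12-month data are locked. Amend the sole-entry sentence in 12.1 to allow for this.
- **Section 3, flow chart:** align the unblinding sentence with the rule in section 3 (duration) and 8.2.2, so that one rule applies throughout.
- **8.3.3 and 11.4:** reconcile the timing of the EDB-only CT with each other and with that rule.

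Cost: a user-rights setting in Castor and a few changes of wording. The operating surgeon may have to complete a few fields, and early patients wait longer to learn their allocation, which 8.2.2 already implies.
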